### Intervention/exposure

The campaign will be generally focused on the appropriate use of antibiotics in upper respiratory tract infections. Problems arising from antibiotic overuse, in particular antibiotic resistance, will be particularly pointed at. On the other side, it will be highlighted that antibiotics are necessary in specific circumstances and should be used when doctors say it. The main instruments of the proposed multifaceted intervention are discussed as follows.

1. Written information material (brochures) targeted at the general population. Specifically, two different types of brochure will be available: type-A brochure will provide general information on benefits and risks of antibiotic therapies; type-B brochures will provide more specific information on three possible clinical situations patients (and doctors) may deal with: antibiotic is necessary and is prescribed; antibiotic is not necessary and is not prescribed; antibiotic may or may not be necessary, so that a "wait and see" period is warranted.

In developing the specific messages, particular attention has been given to the evaluation of key determinants of potentially inappropriate antibiotic use. The occurrence of antimicrobial resistance both at population and individual level, and of side effects, will be particularly targeted. In this regard, the relevance of antibiotic prescribing on individual resistance has been further highlighted by a recent systematic review and meta-analysis [19]. A small group of representative physicians (one per Health District, appointed by their Local Health Authorities) helped identifying the campaign key messages in order to maximize their relevance to the target audiences. Attention will be also given to the editorial appeal and clarity, borrowing communication techniques from commercial marketing to construct an attractive, concise, easy-to-read and recall format.

The brochures will be available in waiting rooms of general practices and local health services (type-A) and will be distributed to patients by general practitioners and paediatricians (type-B). Electronic versions will be available on the web. Translated versions in Albanian, Arab, Chinese, English, French, Polish, Rumanian, Russian will be also posted on the web, so that doctors could print them out to share information with their foreign patients (mostly immigrants).

2. Posters developed through the same methodology as described above (see point 1). Given the nature of this media, specific attention has been given to focusing on few clear messages. Posters will be mainly available in general practices, pharmacies and local health services.

3. Short videos to be transmitted through video terminals in highly accessed places (mainly pharmacies and waiting rooms in surgeries/health services), local TVs and websites of Local Health Authorities.

4. Radio-spots to be transmitted in local radio stations

5. Advertisements and concise articles in local newspapers, written in a scientifically sound but accessible way to the average reader.

6. Web materials/banners in web sites of local newspapers.

7. A newsletter on antibiotic resistance in Emilia-Romagna, available to physicians and pharmacists in the intervention areas.

8. Training courses in counselling strategies, directed to general practitioners and paediatricians to facilitate information transfer on the campaign contents. More specifically, all general practitioners and paediatricians in the intervention areas will get a half-day presentation about the campaign and its instruments, discussing the importance of counselling strategies through examples relevant to the antibiotics campaign. A six-module course will be pilot-tested on about 120-150 physicians on a voluntary basis during the campaign implementation, to improve their ability to convey information and facilitate their patients' behavioural change.

The proposed interventions will be implemented during a 4 month period (November 2011 - February 2012).

### Primary Outcome

Cumulative five-month (November to March) changes in prescribing rates of specific classes of antibiotics in general practice, expressed as DDD per 1000 inhabitants/day.

Data on antibiotic prescriptions (on beta-lactams, cephalosphorins, macrolides, fluoroquinolones, corresponding to J01C, J01D, J01F, J01M atc codes) will be retrieved from regional prescribing databases. They will include NHS prescriptions only from general practitioners (a small part of prescriptions may be made outside NHS on personal prescription books) and will not assess the actual use of antibiotics. In Emilia-Romagna, prescriptions from paediatricians are expressed in pieces and not in DDD, and will be evaluated separately.

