**Methods/design:**

Information will be provided to citizens through several media (posters, local TV, radio and newspapers, video terminals, websites of Local Health Authorities). Brochures with information on expected benefits and risks of antibiotics will be also available, either with direct access in waiting rooms and pharmacies or handed out and mediated by doctors. Physicians and pharmacists will get specific data on local antibiotic resistance. A small group of representative doctors have also actively participated in defining the campaign key messages. A sample of general practitioners and paediatricians will be trained in patient counselling strategies.

The information campaign will be implemented in two Provinces of Emilia-Romagna during the fall-winter season (November 2011-February 2012). Change in the overall prescribing rate of antibiotics (expressed as DDD per 1000 inhabitants/day) in the intervention area will be compared versus other areas in the same Region. Knowledge and attitudes of the general population will be evaluated through a phone and internet survey on a representative sample.

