Within a wider project called ProBA project (progetto Bambini Antibiotici), in 2003 the Health Agency of the Emilia-Romagna Region carried out a survey on 633 paediatricians (453 working as family paediatricians and 180 working in hospitals) and 1388 parents, aimed at evaluating the main determinants of antibiotic prescriptions for children [18]. This survey showed that improving paediatricians' and parents' knowledge on benefits and risks of antibiotics, and suggesting that resistance is a problem at the community but also at the individual level, may favour their more appropriate use.

Starting from these considerations and from local and international experiences on educational campaigns, we propose a study to evaluate the feasibility and effectiveness of a multifaceted intervention on antibiotic prescription in the general population, aimed at reducing it by increasing awareness on risk of unnecessary use, thus reducing patients' requests for unnecessary prescription. The specific objectives are:

• primarily, to reduce the overall volume of antibiotic prescription;

• secondarily, to reduce total costs associated to antibiotic prescriptions; to evaluate knowledge, attitudes and reported behaviours of a sample of citizens on benefits and risks of antibiotic use; and to evaluate trends in antibiotic resistance (in a three year period after the intervention) from sputum, throat swab, urine and blood samples

We consider such intervention of high public health relevance, considering the limited development of new antibiotics and the public health threat due to antibiotic resistance, which is in part accounted for antibiotic use in humans. The proposed intervention will involve citizens, general practitioners and paediatricians in two Provinces of Emilia-Romagna. In addition to promoting the appropriate use of antibiotics, this project will help to evaluate the feasibility of carrying out information campaigns on benefits and risks of medicines promoted by Local Health Authorities, with the collaboration of local physicians.

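### The objective is overall antibiotic volume, but the primary outcome counts four J01 subgroups and no outcome is defined to cover total J01

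*Protocol article*

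**What the plan says.** The Background of the protocol article gives the main objective as "primarily, to reduce the overall volume of antibiotic prescription". The Methods/design part of the Abstract follows suit: "Change in the overall prescribing rate of antibiotics (expressed as DDD per 1000 inhabitants/day) in the intervention area will be compared versus other areas". The Discussion also treats the volume of antibiotics prescribed as the main outcome of interest. None of these places restricts the class.

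The Primary Outcome section is narrower. It measures "changes in prescribing rates of specific classes of antibiotics in general practice", with data "on beta-lactams, cephalosphorins, macrolides, fluoroquinolones, corresponding to J01C, J01D, J01F, J01M atc codes". It gives no reason for choosing these four. It also states two other limits openly: "They will include NHS prescriptions only from general practitioners", and "prescriptions from paediatricians are expressed in pieces and not in DDD, and will be evaluated separately".

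The Secondary outcomes section lists prescribing trends over eighteen months and antibiotic expenditure, without saying which classes they cover. The Sample size calculation uses a baseline of 21.1 DDD per 1000 inhabitants/day, also without a class scope.

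Item 7 of Intervention/exposure provides "A newsletter on antibiotic resistance in Emilia-Romagna, available to physicians and pharmacists in the intervention areas". The opening of Methods/design says that control areas get neither the campaign nor information for physicians.

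**The concern.** The objective and the measured quantity differ in scope. Any J01 subgroup outside the four is left out of the count, however the four are combined, and no other outcome is defined to pick it up.

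This matters if the intervention changes which class is prescribed as well as whether one is prescribed. Resistance information is offered only in the intervention area, so any switching that it causes would be absent from the control areas and would not cancel in the comparison. Each DDD that leaves the four subgroups for another class lowers the primary outcome by one DDD and leaves the total unchanged. Each DDD that moves the other way raises the primary outcome and masks part of a real fall.

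The anticipated effect is small: the Abstract allows for a reduction below 5%, and the Sample size calculation speaks of 3-5% or less. A modest shift between classes could be a noticeable part of such an effect.

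**Working it through.** **Inputs.** From the Sample size calculation: baseline rate 21.1 DDD per 1000 inhabitants/day, and a target reduction of 3-5%. Two assumptions are needed. First, 21.1 is taken as the rate for the four counted subgroups, because the text does not say what it covers. Second, the share s of total J01 that lies outside the four subgroups is not given, so a range is used.

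**Step 1: the target effect in DDD.**
- 3%: 0.03 × 21.1 = 0.633
- 5%: 0.05 × 21.1 = 1.055
- 1%, for a partial artefact: 0.01 × 21.1 = 0.211. This is one third of a 3% effect and one fifth of a 5% effect.

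**Step 2: the uncounted rate.** If the counted rate is 21.1 and the uncounted share of the total is s, the uncounted rate is U = 21.1 × s/(1 − s).
- s = 3%: U = 0.65
- s = 5%: U = 1.11
- s = 10%: U = 2.34

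**Step 3: the rise in uncounted classes that produces a pure artefact.** An apparent reduction of r in the counted rate with no change in the total requires 21.1 × r to move into the uncounted classes. Their relative rise is 21.1r/U = r(1 − s)/s.

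| Assumed share s | 1% artefact | 3% artefact | 5% artefact |
|---|---|---|---|
| 3% | 32% | 97% | 162% |
| 5% | 19% | 57% | 95% |
| 10% | 9% | 27% | 45% |

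At s = 2% the rises for 3% and 5% are 147% and 245%; at s = 15% they are 17% and 28%. The baseline cancels from the formula, so these percentages are the same if 21.1 is instead the total rate. Only the DDD amounts change.

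**Step 4: the opposite direction.** The same percentages, read as falls in the uncounted classes, give the shift that would hide a 1%, 3% or 5% reduction. A fall cannot exceed 100%, so at s = 3% switching could hide at most s/(1 − s) = 0.03/0.97 = 3.1% of the counted rate.

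**Step 5: partial switching.** If the counted rate falls by 5% and a fraction f of that is only moved, the total falls by 5% × (1 − f) × (1 − s). With f = 0.5 this is 2.4% at s = 5% and 2.3% at s = 10%. With f = 0 it is 4.75% and 4.5%.

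The plan states no figure for the uncounted share or for switching, so there is none to reproduce here.

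**The case against.** The restriction is disclosed, and naming classes is a legitimate choice for a campaign centred on upper respiratory infections. If the uncounted agents are little used for those infections, they are unlikely destinations for the courses that the campaign targets. The brochures address whether an antibiotic is needed, and nothing in the article describes advice on which class to choose. At small uncounted shares, a wholly spurious 3-5% effect needs implausibly large rises elsewhere. These arguments stand: they limit the size of the problem and weigh against insisting that the primary outcome be replaced.

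They do not remove the mismatch. The objective and abstract say overall, the outcome does not, and the respiratory focus is never offered as the reason. Methods/design in fact describes a campaign on antibiotic use in general as well as in respiratory infection.

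Three stronger readings are tempting, and the article does not support them:
- **A bias that runs only towards false benefit.** No direction of switching is documented. Resistance data could equally move courses into the four subgroups and hide a benefit.
- **Receipt of the newsletter by every physician.** Item 7 says only that it is made available. The Abstract and Study population do say that physicians will get resistance information, but exposure of each one is not established.
- **Different class scopes for the outcome, the expenditure and the planning rate.** Their scope is unstated. The list in the Primary Outcome section may be meant to define prescription data throughout.

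**Conclusion.** The mismatch is in the printed text and does not depend on any assumption: a result for four subgroups cannot alone show that overall antibiotic volume fell. The resulting distortion is conditional. It requires switching between counted and uncounted classes that differs between intervention and control areas; switching common to both would cancel. Its direction and size cannot be determined from the article, which gives neither an uncounted share nor class-specific advice.

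Under assumed shares of 3-10%, a 1% artefact needs a rise of 9-32% in the uncounted classes, and a 3% artefact needs 27-97%. Switching is therefore a credible contributor to a small effect and an unlikely explanation of the whole of a larger one, unless the uncounted share is substantial. The point is worth correcting because the trial expects a small effect and the correction is cheap.

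**What to change.** In the Primary Outcome section, retrieve all J01 from the same regional database. Prespecify total J01 DDD per 1000 inhabitants/day as a companion outcome, with the four subgroups and the remainder shown as a breakdown. State that a reduction in overall volume will be claimed only if total J01 also falls against control. If the sponsor prefers not to do this, restate the objective and the abstract as the four named classes.

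In either case, state which classes the 21.1 planning rate and the expenditure outcome cover.

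The cost is a wider filter on a query that is already planned, and slight dilution in the total: a 5% fall in the four subgroups with no change elsewhere appears as 4.75% or 4.5% of total J01 at assumed uncounted shares of 5% or 10%. The four-subgroup outcome can remain primary, so its sample size reasoning need not change.

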### Secondary outcomes

- changes in antibiotic prescribing trends in eighteen months

- changes in antibiotic expenditure per 1000 inhabitants/day (comparing to the same November to March period from the previous year)

- knowledge of and attitudes about the campaign messages, through a telephone and internet survey on a sample of the target population.

As for trends in antibiotic resistance, the regional antibiotic surveillance system regularly monitors and will keep monitoring antibiotic resistance through the analysis of blood, throat swab and sputum samples. Considering this circumstance, data about antibiotic resistance will be evaluated in a three year period after the intervention.

### Sample size calculation

In the first three months of 2011, antibiotic prescribing rate in the provinces chosen as possible intervention areas was 21,1 DDD per 1000 inhabitants/day. Ratio of prescribing rates in intervention vs other Provinces in Emilia-Romagna was 1. Standard deviation of the distribution of antibiotic prescribed by general practitioners was about 3,0 in a 2007 dataset of antibiotic prescriptions in the province of Modena. Assuming that ratio of prescribing rates has not changed, that standard deviation of antibiotic prescription is 6,0 (a very conservative doubled figure compared to the 2007 sample) and that is similar in exposed and not exposed areas, it will be possible to observe tiny reductions of antibiotic prescription, and surely meaningful reductions of at least 3-5%, with alfa = 5% and beta = 10%. Potential average economic savings of such reductions would more than offset the fund received to finance the campaign and would be more than three times the out-of-pocket expenses to implement the campaign.

### Statistical analysis

T-test (for continuing variables), chi-square test (for discrete variables), time series analysis and multiple linear regression will be used, the latter to investigate in secondary analyses how specific variables (baseline prescriptions, province, health district, size of assisted population) can affect outcomes. Analysis of covariance (ANCOVA) will be used for evaluating primary outcomes in case relevant baseline imbalances will make statistical adjustment necessary.

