## Methods/design

This study will be a community level, controlled, non randomized trial. An information campaign on benefits and risks of antibiotic use, in general and specifically in upper respiratory infections, will be implemented in the provinces of Modena and Parma, in the Emilia-Romagna region. Regional areas where no campaign will be implemented and no information provided to physicians either will be the control group; the presence of local policies on antibiotics that would possibly alter the comparison with intervention areas will be evaluated immediately before implementing the campaign, so that provinces which may supply misleading data would not be included in the control group. Anyway, prescription of antibiotics in the intervention and control areas shall be similar at baseline (no statistically significant differences).

Considering that the proposed educational intervention will be done at the community level and will be multifaceted using several media, and considering its implementation in only two provinces, we think a randomised design would not add strength to the study validity: in fact, it would be impossible to restrict exposure to half the population and there would be too few units of randomisation. Therefore, we choose a non randomised design which is more feasible given those circumstances.

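### The primary t-test or ANCOVA makes no allowance for allocation by province, with only two exposed provinces, so its p-value, interval and claimed power are too optimistic

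*Protocol article*

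**What the plan says.** - **Allocation** (Protocol article, Methods/design): "This study will be a community level, controlled, non randomized trial". The campaign "will be implemented in the provinces of Modena and Parma, in the Emilia-Romagna region". The authors reject randomisation partly because "there would be too few units of randomisation". The number of control provinces is not fixed, since "provinces which may supply misleading data would not be included in the control group".
- **Endpoint** (Primary Outcome): "Cumulative five-month (November to March) changes in prescribing rates of specific classes of antibiotics in general practice", in DDD per 1000 inhabitants per day.
- **Planning** (Sample size calculation): "Standard deviation of the distribution of antibiotic prescribed by general practitioners was about 3,0", from 2007 data for Modena alone. The SD is doubled to 6.0 and the base rate is 21.1. The section claims that reductions of 3-5% can be shown with alpha 5% and beta 10%. It gives no number of GPs and no between-province variance.
- **Analysis** (Statistical analysis): "T-test (for continuing variables), chi-square test (for discrete variables), time series analysis and multiple linear regression will be used". The regression is assigned to secondary analyses of "how specific variables (baseline prescriptions, province, health district, size of assisted population) can affect outcomes". ANCOVA is used for the primary outcome only if there is relevant baseline imbalance.

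**The concern.** The unit that receives the campaign is the province, and two are exposed. GPs in one province plausibly share health-authority policy, local epidemics and local media, so their prescribing can move together from one winter to the next. A t-test across GPs divides its variance by the number of GPs. The part that a province has in common averages over two exposed provinces only. If that part is left out, the standard error is too small for any positive between-province variance in change.

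Doubling the SD to 6.0 does not protect against this. It enlarges the GP-level noise, which averages out over many GPs, and adds nothing at province level. A chance divergence between provinces in the study winter could therefore be reported as a significant campaign effect. The effect sought is only a few per cent, so modest divergence is enough to matter.

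**Working it through.** **Step 1. The plan's own power claim.** Inputs from Sample size calculation: rate 21.1, SD 6.0, alpha 5% (taken as two-sided, which is not stated), power 90%. Per arm at 1:1, n = 2 × (1.960 + 1.282)² × SD² / difference².
- 3% reduction: difference 0.03 × 21.1 = 0.633, giving 1889 GPs per arm.
- 5% reduction: difference 0.05 × 21.1 = 1.055, giving 680 GPs per arm.

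The claim is arithmetically possible with many hundreds to a few thousand independent GPs. It cannot be verified because no number is given, and it sets the between-province variance to zero.

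**Step 2. Type I error when province is ignored.** Assumptions not in the document: 750 exposed and 2400 control GPs, 2 exposed and 7 control provinces of similar size, and a between-province SD of winter-to-winter change (tau) of 1% or 2% of the rate, that is 0.211 or 0.422 DDD.
- Naive SE = SD × √(1/750 + 1/2400) = 0.251 (SD 6.0) or 0.125 (SD 3.0).
- True SE = √(naive SE² + tau² × (1/2 + 1/7)).
- True type I error = 2 × [1 − Φ(1.96 × naive SE / true SE)].

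| tau | GP SD | Naive SE | True SE | True type I error |
|---|---|---|---|---|
| 0.211 (1%) | 6.0 | 0.251 | 0.303 | 10.4% |
| 0.211 (1%) | 3.0 | 0.125 | 0.211 | 24.3% |
| 0.422 (2%) | 6.0 | 0.251 | 0.421 | 24.3% |
| 0.422 (2%) | 3.0 | 0.125 | 0.361 | 49.5% |

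The implied intraclass correlations, tau² / (tau² + SD²), are 0.0012, 0.0049, 0.0049 and 0.019. None is large.

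**Step 3. Detectable reduction at 90% power, same assumptions.**
- Ignoring province, it is (1.960 + 1.282) × naive SE / 21.1 = 3.9% (SD 6.0) or 1.9% (SD 3.0).
- With province in the error term there are 9 − 2 = 7 degrees of freedom. The non-central t then needs a difference of 3.795 true SEs.
 - SD 6.0: 3.795 × 0.303 / 21.1 = 5.4% (tau 1%), and 3.795 × 0.421 / 21.1 = 7.6% (tau 2%).
 - SD 3.0: 3.8% and 6.5%.

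**Step 4. Does the secondary regression help?** Exposure is an exact function of province. In a model of change with an intercept, a campaign indicator and indicators for nine provinces, the design matrix has 10 columns and rank 9. Fitted that way, the campaign effect is not estimable. The article does not say that it will be fitted that way. Either way, a secondary regression leaves the primary standard error as it was.

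**The case against.** Several points on the other side are fair.

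- **Province is not ignored altogether.** A reader might infer that the plan takes no account of province. It lists province and health district as variables in secondary regression. What is missing is any allowance in the primary comparison.
- **The regression is not shown to fail.** A reader might infer that it cannot return a campaign effect. That follows only if province fixed effects and exposure are fitted together, which the article does not say.
- **Confounding is narrower than all province differences.** A change endpoint, the requirement of similar baselines and the exclusion of provinces with distorting policies largely deal with stable differences. Province-specific change in the study winter remains.
- **The unit is inferred.** The outcome is a population rate and the t-test has no stated unit. GP level is read from the planning SD.
- **Time series analysis is named.** It is not tied to the primary outcome or to any error structure, so it cannot be credited with correcting the standard error.
- **Model detail may sit in a fuller document.** This would settle the matter if the article were silent. Instead it states a test and a power claim that do not fit the allocation it describes.
- **The sizes rest on assumptions.** The SDs of 3.0 and 6.0 describe prescribing levels, whereas tau describes change, so the table only illustrates. The direction holds for any tau above zero.

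**Conclusion.** The point stands in limited form. The comparison named for the primary outcome has no province-level error term although the campaign is allocated to two provinces, so its p-value and interval are too optimistic if provinces differ at all in winter-to-winter change. Under the assumed GP and province counts, a nominal 5% test has a true error of about 10-24% at a between-province SD of 1%, and about 24-49.5% at 2%. These are raised probabilities, and the documents do not support saying that a false positive will occur.

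The 3-5% detectable reduction is unsupported rather than shown to be wrong. In the most favourable clustered case above (SD 3.0, tau 1%) it would be 3.8%, and in the other three it exceeds 5%. The document gives nothing from which to choose between these cases.

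**What to change.** 1. Make the primary analysis a difference-in-differences, or an ANCOVA on change, with exposure at province level. Use a province-level error term (a random province effect or province-level summaries) and degrees of freedom based on the number of provinces. Keep the GP-level t-test as descriptive.
2. Do not fit province fixed effects together with exposure in a model of change.
3. Estimate the between-province variance of winter-to-winter change from earlier winters in the regional prescribing database. Use it to restate the detectable reduction in Sample size calculation, giving the number of provinces and GPs assumed.
4. A permutation check over all pairs of provinces can be added as support only. Its smallest p-value is 1/36 with seven control provinces, but 1/15 with four and 1/10 with three. It therefore cannot reach 5% if controls are dropped to four or fewer.

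**Cost:** no new data, since the regional database already holds what is needed. Intervals become wider and the power statement less favourable. The change puts province-specific variation into the standard error. It does not remove the confounding that comes from having only two exposed provinces, and the report should say so.
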